### Interventions, administration and duration

As part of the trial design, all enrolled patients will receive intervention following embolization of the aneurysm. The UFH group will start intravenous infusion of UFH 24 h after the embolization procedure, upon confirmation of inactive bleeding through head CT scan. The heparin will be administered at a dose of 8–10 U/kg/h, and APTT values will be monitored twice a day for 7 consecutive days. The infusion rate of heparin will be adjusted based on APTT values to maintain it within the range of 35–45 s. In case of APTT values exceeding or falling below the set range, the infusion rate will be decreased or increased by 1 IU and maintained for 12 h. As per FDA standards for the use of low molecular weight heparin, the UFH group will receive subcutaneous injection of prophylactic dose of LMWH (4000 IU) every 12 h for a duration of 1 week starting 24 h after the aneurysm repair.

All experimental UFH is stored in original packaging at 15–30 °C (protected from light and heat). LMWH is stored at 2–8 °C. After opening for more than 24 h, heparin should be discarded. During the administration process, the nursing staff is trained on medication usage and provided with dosing instructions and adverse reaction management plans for both the UFH and LMWH group. To ensure blinding, any communication between the research staff and participants that may reveal group allocation should be avoided. The identity of the medication provider should also not be disclosed.

During hospitalization, both groups of patients will be closely monitored for vital signs and symptoms in the intensive care unit. Platelet-inhibiting agents, nonsteroidal anti-inflammatory drugs, and oral anticoagulants are prohibited during the patient’s treatment period. Physicians will check for interactions with heparin when using other medications and closely monitor bleeding symptoms, adjusting the dosage of heparin or other medications as needed. All patients will receive oral nimodipine, and the blood volume will be maintained in equilibrium. The intracranial pressure of all patients will be monitored with the transducer. Transcranial Doppler (TCD) ultrasound will be performed daily to evaluate for CV, and a weekly follow-up head CT will be performed. In cases where CV or increased intracranial pressure is suspected, urgent head CT angiogram (CTA) or CT scans will be performed for confirmation.

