The assessment of brain edema is mainly based on SEBES score which is mainly based on head CT images and intracranial pressure monitoring values during hospitalization [21]. Head CT scans will be conducted at four stages: at the time of admission (0–2 days after aSAH), after endovascular treatment (4–7 days after aSAH), during hospitalization (7–14 days after aSAH), and before discharge (14–21 days after aSAH). Two blinded neurologists specializing in cerebrovascular diseases will independently evaluate the SEBES value of the patients. The scoring criteria will range from 0 to 4 points. Two pre-determined levels in each hemisphere will be defined, and 1 point will be given for visible sulcal effacement due to the interruption of the gray-white matter connection. Intracranial pressure monitoring will include intracranial ICP monitoring, which is recorded by placing an intracranial probe.

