### Statistical analyses

The data analysis will be carried out with statistical software (SPSS, version 26, SPSS Inc). The covariates between groups will be balanced based on Propensity score matching (PSM). The results of outcomes will be analyzed for differences between the UFH group and LMWH group, using the Student *t*-test, chi-square test, and Mann–Whitney *U* test. For continuous variables, the normality test is estimated using the mean (standard deviation). If parameters are not normally distributed, their median (interquartile range) will be reported. For categorical variables, the proportions of the two groups will be presented. Spearman’s correlation analysis is performed on nonnormal continuous variables. Pearson’s correlation is employed for categorical variables. Variables with differences between the two groups will be analyzed by univariate analysis and multifactor logistic regression. Cox multivariate regression analysis will be used for time-to-events data. All statistical tests are two-sided with *p* < 0.05, crude odds ratio (OR), and confidence intervals (CI) will be calculated. In addition, the number of recruitments, participants lost due to follow-up, violations of the protocols, and other relevant descriptive data will be reported. The missing data will be handled using multiple imputation methodology.

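### Brain edema (SEBES) is compared by tests that ignore the admission SEBES already collected, which costs precision on a secondary outcome

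*Protocol article*

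**What the plan says.** All references are to the protocol article.

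- **Outcome.** Brain edema score is a listed secondary outcome, and the end of the Discussion names brain edema among the effects to be analysed. Under Primary and secondary outcomes: "The scoring criteria will range from 0 to 4 points", and "Two blinded neurologists specializing in cerebrovascular diseases will independently evaluate the SEBES value of the patients".
- **Timing of scans.** "Head CT scans will be conducted at four stages: at the time of admission (0–2 days after aSAH". The three later stages are days 4–7, 7–14 and 14–21 after aSAH.
- **Timing of treatment.** Under Interventions, administration and duration: "The UFH group will start intravenous infusion of UFH 24 h after the embolization procedure". That section places the study intervention after embolization for all enrolled patients.
- **Comparison.** Under Statistical analyses: "The results of outcomes will be analyzed for differences between the UFH group and LMWH group". Three methods are then named for this purpose: "using the Student *t*-test, chi-square test, and Mann–Whitney *U* test".
- **Covariates.** The same section says: "The covariates between groups will be balanced based on Propensity score matching (PSM". It later adds: "Variables with differences between the two groups will be analyzed by univariate analysis and multifactor logistic regression". It names no covariates for either step. The Baseline assessment section lists clinical grades, the modified Fisher score, mRS and laboratory results, but not SEBES or edema.

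**The concern.** The admission SEBES is the same scale as the outcome, measured before study heparin. A pre-treatment value of the outcome is often among its stronger predictors. The stated two-group tests leave that information unused, so the variation in later SEBES that early edema explains stays in the error term.

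Two things follow. The SEBES comparison is less precise than the collected data allow. And if the arms happen to differ in early edema, part of that difference carries into the follow-up comparison, with nothing stated that would remove it.

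**Working it through.** **1. Does anything stated use admission SEBES?**

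- The t, chi-square and Mann–Whitney tests have no baseline term.
- Propensity score matching could reduce a SEBES imbalance only if admission SEBES were a matching variable. No variables are named, and SEBES is not in the baseline list. Matching may also discard randomized patients, which works against precision.
- The logistic regression is triggered by observed differences between groups. It is not described as a model of follow-up SEBES on its admission value.
- Cox regression is reserved for time-to-event data.

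So no adjustment for admission SEBES is stated.

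**2. Inputs.** The article gives no sample size or power figure for SEBES, so there is none to reproduce. The Sample size estimation section gives 228 per group including 10% dropout: 228 × 0.9 = 205 evaluable per arm. The correlation r between admission and later SEBES is not given; 0.3, 0.5 and 0.7 are assumed.

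**3. Precision under linear ANCOVA.** Residual variance is multiplied by 1 − r², the standard error by √(1 − r²), and the effective sample size by 1/(1 − r²).

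| r | 1 − r² | Fall in SE | Effective n multiplier | Unadjusted n per arm for equal precision |
|---|---|---|---|---|
| 0.3 | 0.91 | 4.6% | 1.10 | 205/0.91 = 225 |
| 0.5 | 0.75 | 13.4% | 1.33 | 205/0.75 = 273 |
| 0.7 | 0.51 | 28.6% | 1.96 | 205/0.51 = 402 |

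**4. Power.** In SD units the unadjusted SE is √(2/205) = 0.099. The difference detectable with 80% power (two-sided 5%) is (1.96 + 0.84) × 0.099 = 0.277 SD. With adjustment, the same difference has power 83.6%, 89.9% or 97.5% for r = 0.3, 0.5 or 0.7.

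**5. Check on an ordinal score.** A five-level score was simulated (4,000 runs per scenario, 205 per arm), comparing the Mann–Whitney test with a baseline-adjusted linear model.

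| Observed correlation | Mann–Whitney power | Adjusted power |
|---|---|---|
| about 0.27 | 77% | 80% |
| about 0.45 | 76% | 85% |
| about 0.64 | 77% | 94% |

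Overall type I error was about 5% for both methods.

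**6. Chance imbalance.** A baseline difference at |z| = 1.96 is 1.96 × 0.099 = 0.19 SD. It shifts the unadjusted follow-up difference by r × 0.19, that is 0.06, 0.10 or 0.14 SD. Among simulated trials with imbalance beyond that limit (about 5% of trials), type I error was about 6%, 17% and 27% for Mann–Whitney, against 4%, 5% and 5% adjusted. These rates rest on roughly 200 trials per cell and are approximate.

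**7. Sensitivity to n.** The Randomization and blinding section gives 143 per group instead of 228. That conflict is a separate matter. The percentages in step 3 do not depend on n. With 143 analysed per arm, the detectable difference is 0.331 SD and the baseline difference at |z| = 1.96 is 0.23 SD.

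**The case against.** **The plan does handle covariates.** This stands as a matter of description. A reader might infer that the plan contains no covariate handling at all; the matching and regression sentences rule that out. What is missing is any statement that either step involves admission SEBES.

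**The unadjusted test is valid.** This stands. A reader might infer that chance imbalance biases the result or inflates the overall error rate. Randomization keeps the comparison unbiased over repetitions, and the simulated overall type I error was about 5%. The weakness is conditional, on the minority of trials with a marked imbalance.

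**The gain is assumed.** This stands in part. The correlation is not in the article, and at 0.3 the gain is small. The 1 − r² figures also belong to linear ANCOVA. In a proportional-odds model, adjustment changes the estimand to a conditional odds ratio and generally does not shrink the standard error of the log odds ratio; the gain shows as power.

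**The detail may sit in an unseen analysis plan.** The article assigns no test to SEBES by name, and a separate plan may add an adjusted model. But the article states a method for comparing outcomes, and the point is an improvement on that stated method.

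**SEBES is secondary, in a trial the Background calls exploratory.** This stands and limits the weight of the point.

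**Conclusion.** The point holds as a minor efficiency gain. The stated tests do not use an admission SEBES that is already collected before study heparin, and neither the matching nor the difference-triggered regression is a stated adjustment for it. Under linear ANCOVA the standard error would fall by about 5%, 13% or 29% for an assumed correlation of 0.3, 0.5 or 0.7. The gain is small at the low end and material from about 0.5 upwards. The planned comparison remains valid, and the primary outcome is unaffected.

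**What to change.** In Statistical analyses, add a statement for SEBES:

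- Analyse follow-up SEBES in all randomized patients, without propensity score matching.
- Use ANCOVA with arm and admission SEBES at each of the three later scan stages, or one repeated-measures model across the three stages with the same terms. Choose one of these before unblinded data are seen.
- Take the admission scan as baseline whatever its day. Eligibility allows admission up to 72 h after onset, while the admission scan is labelled days 0–2, so a strict window could leave some patients without a baseline.
- Handle a missing admission score by the multiple imputation already planned.
- Report a baseline-adjusted proportional-odds model and the Mann–Whitney test as sensitivity analyses.

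Also add admission SEBES to the Baseline assessment list. The cost is analysis wording only: no new scans, ratings or enrolment.

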### Sample size estimation

The primary outcome of this study was the incidence of CV. J. Marc’s research indicated that the incidence of CV was 58% and 60% in the groups receiving intravenous unfractionated heparin and subcutaneous low molecular weight heparin, respectively [10]. The hypothesis was that the unfractionated heparin protocol was superior to the subcutaneous low molecular weight heparin injection in reducing the incidence of CV. The sample size of the study was calculated using a bilateral test to achieve a target effect of 0.1 and an α error of 0.05. Considering a dropout rate of 10%, each group would require 228 patients, so a total of 456 participants will be enrolled. The sample size was estimated using PASS (version 15.0.3, NCSS, LLC, Kaysville, Utah, USA).

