UFH accelerates the inactivation of factors Xa and IIa by binding to thrombomodulin III, preventing the obstruction of blood flow by thrombin, and reducing the risk of thrombus formation [8]. LMWH also acts by enhancing the inhibitory activity of antithrombin III (ATIII) on factor Xa, preventing thrombin formation, and reducing the risk of clot [27]. Thrombophilia can induce platelet activation and aggregation, as well as the release of thromboxane A2 and serotonin, which promote vasoconstriction and contribute to CV. Clots can also mediate the release of inflammatory mediators, causing endothelial dysfunction and an imbalance between vasoconstrictive and vasodilatory factors, which can also result in vasospasm. In summary, heparin indirectly inhibits the occurrence of CV by reducing thrombus formation through ATIII.

The choice between LMWH and UFH depends on balancing the antithrombotic effect and bleeding risk. Some non-randomized clinical trials have demonstrated that heparin can reduce the occurrence of ischemia in aSAH. The beneficial effects of heparin are influenced by the type of heparin and the duration of administration. However, there is no significant difference in the incidence of CV-related to LMWH and UFH, suggesting the possibility that heparin may exert beneficial effects through mechanisms other than preventing CV. The impact of heparin on cerebral edema and cerebral venous circulation in aSAH has not been studied.

This randomized trial aims to compare the safety and efficacy of UFH and LMWH in aSAH and analyze their effects on CV, brain edema, and cerebral venous circulation.

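### The 228 per group does not follow from the stated two-sided superiority test of a 0.1 effect at any conventional power; it gives about 53% power for 60% v 50%

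*Protocol article*

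**What the plan says.** Sample size estimation sets a superiority hypothesis: "The hypothesis was that the unfractionated heparin protocol was superior to the subcutaneous low molecular weight heparin injection in reducing the incidence of CV". It cites a retrospective study in which "the incidence of CV was 58% and 60% in the groups receiving intravenous unfractionated heparin and subcutaneous low molecular weight heparin". The calculation is described in one sentence: "The sample size of the study was calculated using a bilateral test to achieve a target effect of 0.1", with an alpha of 0.05. After 10% dropout, "each group would require 228 patients, so a total of 456 participants will be enrolled". The abstract repeats 228 and 456. Statistical analyses confirms the sidedness: "All statistical tests are two-sided with" a 0.05 threshold.

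The paragraph does not state the power, the scale of the 0.1, or the two rates that differ by 0.1. Randomization and blinding gives another size, 286 patients with 143 per group, and builds the allocation list on it.

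**The concern.** Once the test, effect, alpha, dropout and group size are given, only the base rate and the power remain open. The cited rates point to a base near 60%, so the implied power can be worked out, and it is well below 80%.

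The paragraph presents 228 as the number required. A reader will assume that the trial has a good chance of showing a 10-point reduction in cerebral vasospasm (CV). If the chance is about one in two, a non-significant result is likely even when the target effect is real, and it could be misread as showing that the two regimens are alike.

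**Working it through.** **Inputs.** From the article: two-sided alpha 0.05, effect 0.1, cited rates 58% and 60%, 10% dropout, 1:1 allocation, 228 enrolled per group. Evaluable per group: 228 × 0.9 = 205.2, taken as 205. Assumptions: 0.1 is an absolute risk difference; the control rate is 60% (other bases are tried below); conventional power is 80% or 90%.

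**1. Attempt to reproduce 228.** Pooled two-proportion formula, with p̄ the mean of the two rates and d their difference:

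n = [z(α/2)·√(2p̄(1−p̄)) + z(β)·√(p1(1−p1) + p2(1−p2))]² / d²

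For 60% v 50%, p̄ = 0.55:
- 80% power: [1.960·√0.495 + 0.842·√0.49]² / 0.01 = (1.379 + 0.589)² / 0.01 = 387.3, so 388 per arm; 388/0.9 = 431.1.
- 90% power: (1.379 + 0.897)² / 0.01 = 518.0, so 519 per arm; 519/0.9 = 576.7.

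Other bases at 80% power, evaluable per arm: 58% v 48% needs 390, 68% v 58% needs 365, 70% v 60% needs 356. A one-sided test of 60% v 50% still needs 305. Reading 0.1 as Cohen's w needs 785 in total, about 393 per arm. Reading it as Cohen's h needs 1,570 per arm. None comes near 205 evaluable or 228 enrolled.

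**2. Power that 228 gives.** Power = Φ[(d − 1.960·s0)/s1], with s0 = √(2p̄(1−p̄)/n) and s1 = √((p1(1−p1) + p2(1−p2))/n).
- 60% v 50%, n = 205: s0 = 0.04914, s1 = 0.04889; (0.1 − 0.09631)/0.04889 = 0.075; power 53.0%.
- The same with n = 228: 57.4%.
- Other bases at n = 205: 52.7% (58% v 48%), 55.5% (68% v 58%), 56.5% (70% v 60%). The most favourable case tried, 70% v 60% with all 228 analysed, gives 61.0%.

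**3. Detectable difference.** With 205 per arm and a 60% control rate, power reaches 80% at a difference of 13.8 points.

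**4. The cited difference, for context.** 60% − 58% = 2 points, one fifth of the target. Power at n = 205 is 6.1% in the favourable direction and 7.0% counting both tails.

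**5. Calculations that land near the stated figures.**
- Two-sided 58% v 48%, 80% power, with continuity correction: 410 per group; 410/0.9 = 455.6, so 456 per group. This equals the stated total.
- Non-inferiority, margin 0.10, true rates 58% v 60%, one-sided alpha 0.05, 80% power: (1.645 + 0.842)² × (0.58·0.42 + 0.60·0.40)/(0.10 + 0.02)² = 207.6; × 1.1 = 228.4; /0.9 = 230.7.

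**6. The other stated size.** With 143 analysed per group, power for 60% v 50% is 39.7%.

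**The case against.** The strongest objection is that the paragraph states no power, so 228 cannot be shown wrong. That stands in part: the mismatch is with 80% and 90% power near the cited rates, not with a power the authors declared. But the stated inputs then imply a power of 53% to 61%, and a size described as required needs a better basis than that.

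A second objection is that the Background calls the trial exploratory. That could justify low power, but Sample size estimation gives a directional superiority hypothesis and a formal calculation, and does not say that lower power was accepted.

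Three stronger readings are tempting and not supported.
- A reader might infer that power of 6–7% at the cited difference is itself the error. It is not: the calculation targets 0.1, and a target larger than an earlier difference is a design choice. The Background also reports, from the same source, a significant fall in clinical vasospasm, and that source is not available here. What stands is that the two cited rates do not support a target of 0.1.
- A reader might infer that a non-inferiority calculation was run. It reaches 228 only if 207.6 is left unrounded, multiplied by 1.1 and rounded down, and it contradicts the stated test and hypothesis. The continuity-corrected superiority calculation matches the total of 456 and keeps the stated test, effect, alpha and dropout, but it assumes a 58% base and 80% power. The document cannot decide between them.
- The Discussion's remark that "there is no significant difference in the incidence of CV-related to LMWH and UFH" might be read as bearing on the calculation. It is a general comment on the literature and does not.

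**Conclusion.** The point holds: 228 per group does not follow from a two-sided superiority test of a 10-point difference near the cited rates at 80% or 90% power. For 60% v 50% the requirement is 388 evaluable per arm at 80% power, against about 205 available, and the power obtained is about 53%. The 80% detectable difference is about 13.8 points.

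This rests on reading 0.1 as an absolute difference, on a control rate near 60%, and on 10% loss. Changing the base within the range tried, or analysing all 228, moves power only between 53% and 61%. The document does not show how 228 arose, and it does not establish that 456 must be either kept or raised.

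**What to change.** Check the PASS run first, looking for two possible slips: a per-group 456 entered as the total, and a non-inferiority module used for a superiority hypothesis.

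Then restate Sample size estimation with the base rate, the scale of the 0.1, the test and the true power. Either resize the trial to the intended power or justify the lower one. If 456 is kept, wording such as this would do: with 228 enrolled and about 205 evaluable per group, a 60% control rate and a two-sided 5% test, power is about 53% for a 10-point reduction and 80% for about 13.8 points; a non-significant result does not show equivalence.

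Reconcile this with the 286 (143 per group) under Randomization and blinding, including the allocation list built on it, so that one size governs the trial.

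If 456 is kept, the cost is one reworded paragraph, the matching correction to the randomization text, and a less favourable stated power. Resizing would cost more patients; for 60% v 50% at 80% power, about 431 per group with dropout.

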### Statistical analyses

The data analysis will be carried out with statistical software (SPSS, version 26, SPSS Inc). The covariates between groups will be balanced based on Propensity score matching (PSM). The results of outcomes will be analyzed for differences between the UFH group and LMWH group, using the Student *t*-test, chi-square test, and Mann–Whitney *U* test. For continuous variables, the normality test is estimated using the mean (standard deviation). If parameters are not normally distributed, their median (interquartile range) will be reported. For categorical variables, the proportions of the two groups will be presented. Spearman’s correlation analysis is performed on nonnormal continuous variables. Pearson’s correlation is employed for categorical variables. Variables with differences between the two groups will be analyzed by univariate analysis and multifactor logistic regression. Cox multivariate regression analysis will be used for time-to-events data. All statistical tests are two-sided with *p* < 0.05, crude odds ratio (OR), and confidence intervals (CI) will be calculated. In addition, the number of recruitments, participants lost due to follow-up, violations of the protocols, and other relevant descriptive data will be reported. The missing data will be handled using multiple imputation methodology.

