### Study intervention

#### Randomization and blinding

This is a randomized, double-blind, controlled trial in which participants will be randomly assigned to one of two groups: the UFH group and the LMWH group. Participants will be unaware of their treatment assignment. The study aims to recruit 286 patients, with 143 patients in each group. Randomization will be conducted using a randomization sequence generated by R software. The specific method for randomization is as follows: install and load the rlist package, generate participant IDs, and use the shuffle function to randomize the participant IDs. The randomized ID data will then be arranged in order, with IDs 1–143 assigned to the UFH group and IDs 144–286 assigned to the LMWH group. Randomization will be performed by an assistant who is not involved in the study, and detailed information regarding the allocation will be kept in sealed envelopes labeled with a sequence number and will not be disclosed to participants. Data evaluation and analysis will be conducted by independent researchers under the supervision of an independent statistician. Participants, data-collecting researchers, and follow-up teams are precluded from making group allocations.

Severe adverse events include shock caused by thrombocytopenia and cerebral hemorrhage. If a severe adverse event occurs, the intervention should be discontinued if necessary, and the patient should receive appropriate rescue treatment. Blinding will be opened, and the event will be reported to the institutional review board. Compensation will be provided to subjects who are injured as a result of participating in the trial. Medical data will still be collected and analyzed. If a general adverse event occurs, patients do not need to be unblinded.

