### Outcome assessments

#### Baseline assessment

Baseline variables encompass demographic information (gender, age, ethnicity, prior medical history, personal life history), comorbidities, vital signs (blood pressure, heart rate, respiratory rate), concomitant medication, surgical intervention (e.g., decompressive craniectomy), and results of the laboratory tests. In addition, Hunt-Hess scales [14] and World Federation of Neurosurgery Societies (WFNS) [15] grade were used to assess the severity of clinical symptoms. Modified Fisher score [16] was employed to evaluate the degree of CV. Assessment of functional independence was performed by the Modified Rankin Scale (mRS) [17]. All clinical baseline data were conducted upon admission and during hospitalization by two researchers who were unaware of the group assignment.

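### The plan balances randomized arms by propensity score matching and picks regression variables by observed difference. This can drop randomized patients and leaves post-treatment covariates possible.

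*Protocol article*

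**What the plan says.** All places are in the protocol article.

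- **Design (Randomization and blinding):** "This is a randomized, double-blind, controlled trial in which participants will be randomly assigned to one of two groups".
- **Matching (Statistical analyses):** "The covariates between groups will be balanced based on Propensity score matching (PSM"). The next sentence compares outcomes between the arms by t-test, chi-square and Mann–Whitney tests. Matching is not labelled a sensitivity analysis, and no analysis of all randomized patients is named.
- **Choice of model variables (Statistical analyses):** "Variables with differences between the two groups will be analyzed by univariate analysis and multifactor logistic regression".
- **Baseline window (Baseline assessment):** "All clinical baseline data were conducted upon admission and during hospitalization by two researchers who were unaware of the group assignment". The listed items include "concomitant medication, surgical intervention (e.g., decompressive craniectomy), and results of the laboratory tests".
- **Start of treatment (Interventions, administration and duration):** "The UFH group will start intravenous infusion of UFH 24 h after the embolization procedure", with APTT monitoring for 7 days.
- **Size (Sample size estimation):** 228 per group and 456 in total, with a 10% dropout allowance. There is no allowance for unmatched patients. Randomization and blinding gives 286 in total.

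**The concern.** Propensity score matching repairs confounding from non-random assignment. In a properly randomized trial the arms differ at baseline only by chance, and the standard error and p-value of the randomized comparison already allow for that. Matching therefore solves a problem the design does not have, and it can cost patients. If some patients find no match, the comparison is no longer between the groups that randomization formed.

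The second rule chooses model variables because they happen to differ between arms. Chance imbalance does not show which variables predict vasospasm, and the choice is made after the data are seen.

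The third part is timing. Baseline data may come from the hospital stay as well as from admission, and treatment runs in hospital. Concomitant medication, decompressive craniectomy and laboratory results can respond to vasospasm, bleeding or heparin. The article itself ties emergency craniotomy to severe cerebral hemorrhage (Safety assessments) and defines heparin-induced thrombocytopenia by a fall in platelet count (Primary and secondary outcomes). Matching or adjusting on such values would condition on consequences of treatment. Blinded data collectors do not prevent this.

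**Working it through.** **Inputs from the article.** 228 per group, 10% dropout, two-sided test, α = 0.05, target effect 0.1. The cited rates are: "the incidence of CV was 58% and 60% in the groups receiving intravenous unfractionated heparin and subcutaneous low molecular weight heparin, respectively".

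**Assumptions.** The target effect is read as a 10-point difference, 60% v 50%. Matching is 1:1 nearest-neighbour without replacement, with a caliper of 0.2 SD of the logit and 5 to 20 covariates.

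**1. The plan's own figure.** 228 × 0.9 = 205 evaluable per arm. Power is not stated. At 80% power, 60% v 50% needs 388 per arm, or 388 / 0.9 = 432 with dropout, so 228 does not reproduce on these inputs. That is a separate matter. Here 205 per arm is only the starting point.

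**2. Power with everyone kept.**
Power = Φ{[Δ√n − 1.96·√(2p̄(1−p̄))] / √(p₁(1−p₁) + p₂(1−p₂))}, with Δ = 0.1 and p̄ = 0.55.
For n = 205: (0.1 × 14.318 − 1.96 × 0.7036) / 0.7 = 0.075, so power is 53%. With 58% v 48% it is also 53%. With 143 enrolled per arm (129 evaluable) it is 36%.

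**3. Patients kept after matching (simulation, 205 per arm).**

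| Covariates | Share kept | Power, all patients | Power, matched |
|---|---|---|---|
| 6 / 12 / 20 (58% v 48%, 800 runs each) | 87 / 84 / 81% | 56 / 55 / 56% | 51 / 47 / 45% |
| 5 / 10 / 15 / 20 (60% v 50%, 1000 runs each) | 87 / 85 / 83 / 81% | 51–56% | 43–48% |

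Simulation error is about 1.6 to 1.8 points. The formula agrees: 184 pairs give 48.7%, 174 give 46.6% and 164 give 44.4%. So 13–19% of patients are lost and power is about 43–51%.

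**4. Sensitivity to the caliper.** 1:1 matching of equal arms with no caliper kept 100%. A 0.5 SD caliper kept 83–92% (20 down to 3 covariates).

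**5. Adjustment instead of matching, all 205 per arm kept.** Simulated power is 52–54% if no covariate is prognostic, 57–58% with three moderately prognostic covariates, and 62–64% with two stronger ones (assumed log-odds ratios 0.8 and 0.6 per SD).

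**6. The differences rule.** If it means p < 0.05 and the variables are independent (both assumed), the chance that at least one differs is 1 − 0.95^k. This is 23% for k = 5, 40% for k = 10 and 64% for k = 20.

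**7. Illustration of post-treatment adjustment.** Assume a variable that arises after treatment starts in 12% (UFH) v 20% (LMWH), with log-odds 2.0 for vasospasm, and 60% vasospasm on LMWH.
- LMWH: 0.20 × 0.892 + 0.80 × 0.527 = 0.60, odds 1.50.
- UFH with no other effect: 0.12 × 0.892 + 0.88 × 0.527 = 0.571, odds 1.33.
- Total odds ratio 1.33 / 1.50 = 0.89. Adjusted for the variable it is 1.00.

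If the UFH rate is instead 50%, the total odds ratio is 0.67 and the adjusted one 0.74. Both move towards no effect.

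**The case against.** Four stronger readings are tempting, and the article does not support them.

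- **That matching will discard patients.** No ratio, caliper or covariate list is given. With equal arms and no caliper almost nobody is lost, so the loss is possible and not certain. This does not rescue the method: caliper-free matching keeps nearly the same patients and so balances little.
- **That the regression is the primary treatment estimate.** The article compares outcomes by simple tests and calculates crude odds ratios. The sentence on variables with differences is ambiguous and may describe a secondary analysis of factors. The primary comparison is left open mainly through the undefined matching set.
- **That the plan matches on craniectomy or later medication.** The article never links the baseline list to the matching model and does not say which item is recorded when. Part of the hospital stay precedes the first dose. Post-treatment values are permitted, not planned.
- **That sizing on a difference and reporting an odds ratio is an error.** It is common practice and no fault here.

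The power figures are also conditional. They take 456 enrolled, whereas another section says 286, and the 62–64% after adjustment is a favourable case.

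An analysis plan could supply the ratio and caliper, but these would not make matching suitable for randomized arms. The article states the method outright, so this is not a detail left for later.

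**Conclusion.** The concern holds in this limited form. The article plans a method that does not suit a randomized comparison, names no analysis of all randomized patients, and lets observed differences choose model variables from a baseline set that may reach past the start of treatment.

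Under the stated assumptions (0.2 SD caliper, 5 to 20 covariates, 205 evaluable per arm, a 10-point difference) matching drops about 13–19% of patients and takes power from about 53% to about 43–51%. With no caliper the loss is near zero. Prespecified adjustment keeps everyone and gives about 52–64%, depending on how prognostic the covariates are. The bias from post-treatment covariates cannot be sized from the article; the odds ratios in step 7 only show how it could arise. The correction is needed because it concerns the comparison that yields the primary result.

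**What to change.** 1. Delete the propensity score matching sentence and the rule on variables with differences.
2. State that the primary analysis compares vasospasm between the arms in all randomized patients, as allocated.
3. If adjustment is wanted, name a short list of prognostic covariates measured before randomization, for example age, WFNS grade and modified Fisher score. Take the modified Fisher score from the admission CT only, because Baseline assessment describes it as a measure of the degree of vasospasm, which is the primary outcome.
4. Restrict baseline to values recorded before randomization. Report later medication, surgery and laboratory results as events during follow-up and keep them out of the primary model.

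**Cost.** Analysis wording only. The example covariates are already on the baseline list, provided that their admission values can be told apart from later ones. The change should be made before unblinded data are seen.
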